**Fig. 2 Fig2:**
[figure not shown]
The Seniors Exercise Park

The equipment is located outdoors and safe to use by any age group. Our previous studies found the exercise park to be safe for older people (aged 60 years and over, including with increased risk of falls) with no adverse events [17, 19]. The exercise park equipment was installed in 2019 at Liscombe House, Leith Park, and is owned and managed by the aged-care facility.

#### The Seniors Exercise Park program

##### 12-week structured supervised exercise program

Participants will undergo a 12-week supervised exercise intervention program twice a week using the Seniors Exercise Park. Participants will perform exercises that focus on strength, balance, coordination, mobility and flexibility as detailed in our previous work [15, 24]. Examples of the exercises can be found here https://youtu.be/PaYuCMtnlYk. The exercise park sessions will be provided two times a week (each class approximately 1 to 1.5 h duration) and will be supervised by a qualified accredited exercise physiologist or physiotherapist with the assistance of another supervisor (aged-care staff; physiotherapist/diversional therapist). Each session will consist of 5–7 min warm-up exercises, followed by 45–75 min on the equipment stations, and will conclude with 5–7 min of cool down exercises. The exercise classes will include 3–4 participants and will be circuit-based. To maximise social interaction and enjoyment, morning/afternoon tea will be organised following the exercise sessions.

##### Exercise intensity

The exercise progression will follow the guidelines of the Australian Position Statement on exercise for falls prevention [42]. The initial level of the exercise difficulty will be tailored to the capabilities of the participant with the primary consideration of safety. Adjustment of the exercises (i.e. increase in intensity and difficulty) will be made based on the individual participant progression. Additional exercises will be gradually introduced to the participants every 1–2 weeks. The supervising staff will determine timing of exercise progression based on clinical judgement including consideration of levels of apparent fatigue and exercise difficulty. Participants will also be asked how difficult the exercise was for them and how they generally feel when they perform it, which will further assist the staff to adjust the exercise to the individual.

##### Individual and group exercise progression

Each exercise station will include two exercises and will be performed twice by each participant. Two participants will be allocated in each station, such that each participant will perform one at a time and will swap over. Participants will be given a resting period of 30–60 s (or longer if needed), which will be adjusted according to program progression. The duration of each exercise will also increase based on program progression. Participants will be allowed to have as many breaks as necessary to keep them performing the exercises with good technique and proper form. Examples of exercise duration, rest and progression are given in Table 2. The general exercise program structure will follow our previous published protocol [15, 24]; however, given this is a feasibility study with a different clinical cohort, we anticipate modifications in the program and will be recording and reporting any variations.

**Table 2 Tab2:** Duration of exercise time, rest time and progression

Week number	Set time	Rest time
1 to 2	60 s	30–60 s to change over and rest
3 to 5	60 s	≤ 30 s change over and rest
6 to 9	75 s	≤ 30 s change over and rest
10 to 12	90 s	≤ 30 s change over and rest

#### Exercise uptake and physical activity maintenance

##### Maintenance phase: 12–24 weeks post-baseline

After completion of the 12-week program, it is expected that participants will be familiar with the equipment and the exercises and therefore able to exercise more independently. Pre-scheduled sessions will be available for participants to access and use the Seniors Exercise Park under supervision (aged-care/diversional therapist staff from the facility). To facilitate independence and empowerment, participants will be encouraged to exercise independently (supervised but unstructured sessions). Small exercise cards with graphic images of the required exercises will be placed in each exercise station to aid participants to progress through the stations.

### Control group

Participants from the control group will be given the opportunity to participate in organised recreation and leisure-based group activities, such as art or music, that are run by the Diversional Therapist staff at the aged-care facility. The exercise intervention provided is in addition to what is already provided and is not replacing any other physical activities, therefore control participants will not be withheld from receiving physical activity programs or any related one-on-one physiotherapist sessions.

### Safety considerations and adverse events

#### Wandering behavior

Wandering or ‘walking off’ behavior is common amongst people living with dementia and is defined as the inability of older adults with dementia to find their way while pursuing a need or goal [43]. Walking off may occur during the delivery of the exercise program. A staff member from the facility (or the exercise instructor) will be taking the participants to and from the exercise park area at the beginning and at the completion of the session. Importantly, the Seniors Exercise Park is fenced with a locked gate. If deemed necessary, during the exercise session delivery, the gate will be shut to prevent participants from leaving the area. The area has a seated bench and resting chairs where participants can sit down and rest. Participants who walk off will be intermittently encouraged to re-join the exercise group.

#### Weather conditions

In extreme weather conditions (e.g. heavy rain, extreme hot days (above 35 °C)) if deemed by the exercise instructor as unsafe to exercise, sessions will be cancelled. In summer in Melbourne, classes will be conducted in the morning and late afternoon (to avoid the high temperatures during the middle of the day), and shade-cloth cover and/or other sun-smart behaviors will be facilitated. Sunscreen and water will be available from the exercise instructor at supervised sessions. In circumstances where sessions are cancelled, re-schedule of sessions will be attempted (if weather and staff/participant availability permit); or make up sessions will be organised towards the end of the program.

#### Adverse events

The exercise program is designed to be moderate intensity, where exercise difficulty is tailored to each participant based on their abilities. Given that we aim to test the feasibility and safety of the exercise program in residents living with dementia, we expect that adjustments will occur based on how the participants respond at each session.

##### Muscle soreness/joint pain/discomfort

Following the exercise sessions, some muscle soreness is anticipated and is a typical response of the body to exercise in people who have done little, if any recent exercise, or people who are performing an unfamiliar type of exercise. Instances of severe muscle soreness (muscles soreness that does not settle within a few days) reported by the participant will be recorded.

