### Design and setting

This study is a feasibility pilot randomised controlled trial with pre-post evaluation. Older people aged 60 years and over who reside in Leith Park aged-care facility in Melbourne and who experience symptoms of dementia (such as memory loss or forgetfulness) consistent with a diagnosis of dementia and/or have a formal diagnosis of dementia will be recruited. Participants will be randomised to either an exercise intervention group (Seniors Exercise Park program) or to a control group. Participants from the intervention group will undergo a 12-week supervised structured physical activity program using the Seniors Exercise Park outdoor equipment, followed by a 12-week maintenance phase (unstructured independent exercise). Participants from the control group will be given the opportunity to participate in organised recreation and leisure-based group activities such as art and music (as part of the aged-care facility’s standard care). All participants will be assessed at baseline, 3 months and 6 months follow-up as detailed in Fig. 1.

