### Procedure

At the baseline assessment, the following information will be recorded via semi-structured interview with the participant: demographic characteristics (age, gender), anthropometric measures (height and weight), previous medical history, current medication usage, socioeconomic and cultural background information (e.g. employment, level of education, country of birth, years of residency in Australia) and falls history (number of falls in the past 12 months). Information about medical history, medication usage, dementia diagnosis and falls history will also be extracted from the participant’s medical record kept onsite, to cross-check and to optimise accurate data collection.

At baseline, 3 months and 6 months participants will undergo a comprehensive suite of physical function (strength, balance, functional mobility) tests, psychosocial (quality of life, loneliness, depression) questionnaires, falls risk assessment and falls history assessments. Randomisation will take place at the completion of the baseline assessment. Those who are randomised to the exercise intervention group will be required to obtain a medical clearance from the General Practitioner on-site prior to commencing participation in the exercise program. Study design and study procedures and assessments are provided in Fig. 1 and Table 1 respectively.

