### Assessments

#### Primary outcome

The primary outcomes for this study are the feasibility, safety and supervisory needs associated with the program:

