##### Safety

Safety will be assessed based on the following: any falls that occur during the exercise delivery sessions, any adverse events (joint/muscle pain during the exercise, or as a result of the exercise sessions), serious adverse events (any report of difficulty breathing that does not settle quickly with rest, new or unrelenting chest pain, or acute changes in the level of consciousness during the session where a medical emergency procedure is required). Any incidents and or events will be recorded at each session.

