##### Joint pain

It is anticipated that some participants might have pre-existing musculoskeletal comorbidities such as joint arthritis or join pain (for example at the knee or hip). In instances where participants report increased joint pain, the exercise will be reviewed and modified. Any severe pain (more than 7 on a 0–10 pain scale) that is persistent over 2–3 consecutive sessions, will be noted and the exercise program will be modified for that participant.

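### For soreness and joint pain arising after or between sessions, participant report is the only stated source, in residents with memory impairment, although pain after sessions counts in a primary safety outcome

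*Protocol article*

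**What the plan says.** The Primary outcome section states: "The primary outcomes for this study are the feasibility, safety and supervisory needs associated with the program". Under Safety, the events include "any adverse events (joint/muscle pain during the exercise, or as a result of the exercise sessions"), and "Any incidents and or events will be recorded at each session". The Statistical analysis section counts muscle or joint pain of any degree, whether it occurs in a session or afterwards.

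The Adverse events subsections say where the information comes from:

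- Muscle soreness/joint pain/discomfort: "Instances of severe muscle soreness (muscles soreness that does not settle within a few days) reported by the participant will be recorded".
- Joint pain: "In instances where participants report increased joint pain, the exercise will be reviewed and modified". A further sentence covers the severe cases: "Any severe pain (more than 7 on a 0–10 pain scale) that is persistent over 2–3 consecutive sessions, will be noted". It names no reporter.

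The population is described under Design and setting as residents with "symptoms of dementia (such as memory loss or forgetfulness") consistent with dementia, a formal diagnosis, or both. The eligibility and Randomisation sections admit sMMSE scores above 10 and up to 24. The Recruitment and consent section allows residents without capacity to consent, through a nominated representative.

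At baseline, the Procedure section has medical history, medication, diagnosis and falls history extracted from the on-site record as well, "to cross-check and to optimise accurate data collection".

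**The concern.** Pain that begins after the resident leaves the park reaches the data only if the resident raises it. The severe-soreness definition adds to the difficulty: the resident must not only feel sore but also convey that it has lasted for some days. People chosen for impaired memory are poorly placed to do that, and no second source is stated.

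Pain that is not voiced is counted as no event. The error therefore runs one way, towards a lower event rate, in a trial whose purpose includes judging whether the program is safe and suitable for this group. With about 12 residents exposed to the sessions, one or two missed cases would change the safety summary noticeably.

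**Working it through.** **1. The plan's own figure.** The only sample-size figure is 24 recruited with about 15% dropout: 24 × (1 − 0.15) = 20.4, which agrees with the stated 20 completers. The document gives no pain rate and no reporting rate, so the rest is a comparison of passages followed by an illustration.

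**2. Which sections could capture pain arising between sessions?**

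- *Safety* says that events are recorded at each session. That fixes when they are written down, not who identifies pain that arose since the last session.
- *Exercise intensity* has staff ask how hard an exercise was and how the participant feels while doing it. This can pick up pain in the session. It does not ask about the preceding days.
- *Physical activity program optimization* provides for post-session field notes on program variations, behavior and other relevant matters. Pain is not named. Monitoring in the maintenance phase names activity and duration.
- *Procedure* uses the on-site record for baseline information only.
- *Muscle soreness* and *Joint pain* name the participant as the one who reports.

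No section states a staff or record route for pain that arises between sessions.

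**3. Interval between contacts.** Sessions are twice weekly, so the two gaps in a week add up to 7 days and at least one is 7/2 = 3.5 days or longer.

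**4. Illustration of what incomplete reporting would do.** Inputs: n = 12 in the exercise group (Sample size section); s = the fraction of residents with an event whose event is reported (assumed; the document gives none); p = true per-person rate (assumed 25%).

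- Upper bound when 0 of 12 are captured, one-sided 95%: (1 − 0.05^(1/12)) / s = 0.2209 / s.
- Expected number captured: 12 × 0.25 × s.
- Chance of capturing at least one: 1 − (1 − 0.25 s)^12.

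| s (assumed) | Upper bound on true rate if 0/12 | Expected captured at p = 25% | Chance of at least one |
|---|---|---|---|
| 1.00 | 22.1% | 3.0 | 96.8% |
| 0.75 | 29.5% | 2.25 | 91.7% |
| 0.50 | 44.2% | 1.5 | 79.9% |
| 0.30 | 73.6% | 0.9 | 60.8% |

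The table shows direction and sensitivity. It does not estimate the bias in this trial.

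**The case against.** The strongest reply is that the article does not confine pain data to late self-report. Events are recorded at every session, two staff supervise groups of 3–4, participants are asked how they feel during exercise, and the severe joint-pain sentence names no reporter. This stands for pain during a session. A reader might infer that all pain is captured only if the resident mentions it days later. The document does not support that: the few days in the soreness sentence define severity, not the time of the report.

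Second, soreness that has not settled may still be present at the next session, so it can be reported as a current symptom, and joint pain persisting over consecutive sessions can be rated each time. This weakens the recall argument but does not remove it. The resident must still voice the symptom and convey its duration, and no standard question prompts this.

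Third, the contrast with other measures is limited. The record cross-check is a baseline procedure, the staff-rated scales are staff-rated by design, and the trial uses self-report for mood, enjoyment and quality of life. That is fair. The cross-check shows only that the on-site record is available to the researchers.

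Fourth, who is asked about adverse events may be left to a full protocol or case report form. That would answer a silence. Here the article states the source.

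Finally, the Safety and Statistical analysis sections count any pain, whereas the Adverse events subsections specify recording for severe or persistent cases. Those passages must be reconciled, but that is a separate matter: aligning the threshold would not add a second source.

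**Conclusion.** The point holds for muscle soreness and joint pain arising after or between sessions. Participant report is the only source stated for them, the participants have memory impairment, and such pain belongs to a primary safety outcome. Under-ascertainment is likely, and it would make the program look safer than it is.

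This rests on two assumptions: that some residents will not recall or voice such pain, and that supervising staff have no unstated routine for finding it. The size cannot be calculated, because the document gives neither a pain rate nor a reporting rate; the illustrative figures depend on assumed values of both. A reader might also infer that the loss will be greatest in the moderate stratum (sMMSE above 10 and below 20). That is plausible, but no data by stratum are given, so it should not be stated as a finding. The change is worth making because it is cheap, not because a large bias has been shown.

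**What to change.** Amend the Safety and Muscle soreness sections so that, at the start of each session, information on pain or soreness since the last session is sought from three sources:

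- the resident, by a standard question;
- the facility supervisor already attending;
- the resident's on-site notes since the last session.

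Record which source identified each event and report counts by source. A breakdown by sMMSE stratum should be descriptive only, since about 12 exercisers are divided between two strata.

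This changes data capture and nothing else. The rule in the Joint pain section for modifying exercise stays as it is.

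The cost is protocol wording and a few minutes per session. Some pain unrelated to exercise will also be captured, so the reported rate will be less favourable; the record of source will help readers interpret it.

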##### Joint pain

It is anticipated that some participants might have pre-existing musculoskeletal comorbidities such as joint arthritis or join pain (for example at the knee or hip). In instances where participants report increased joint pain, the exercise will be reviewed and modified. Any severe pain (more than 7 on a 0–10 pain scale) that is persistent over 2–3 consecutive sessions, will be noted and the exercise program will be modified for that participant.

##### Falls

Any falls occurring during the exercise sessions will be recorded. A fall is defined as an event when the participant ‘inadvertently comes to rest on the ground, floor or other lower level’ (WHO Global Report on Falls Prevention in Older Age [44]).

##### Cardiorespiratory adverse reaction

Any report of difficulty breathing that does not settle quickly with rest, new or unrelenting chest pain, or acute changes in the level of consciousness during the session, may precede a serious medical emergency. A potentially serious event will be defined if the participant reported difficulty breathing but symptoms settled quickly with rest and their clinical signs (respiration rate, heart rate, oxygen saturation) remain normal. A serious adverse event will be defined if symptoms have not settled and medical emergency care was required.

##### Data storage, management and dissemination

All participants will be assigned a code/ID. The information will only be accessible to the research team. All hard copies of the assessments and questionnaires will include participants code/ID and not their personal information and will be kept on a locked cabinet in a locked research team office. Information stored on computer files will be password protected. Field notes, such as adherence sheets and other information that will be recorded during the exercise session delivery will include minimal personal identification (e.g. name of participant) but without any sensitive information or any identification code linking to the participants. These field notes will need to be used on a regular basis and will be kept with the researchers or in a secure cabinet at the aged-care facility.

At the completion of the project, the publications or research reports will be available to participants or their consenting person on request. Copies of the publications will be given to the aged-care staff who will also be able to share it with the residents. A one page plain language summary of the project results will be provided to all study participants and /or their family.

##### Cleaning and hygiene practice—a standard precaution for infection control (including COVID-19)

All staff will practice good hand hygiene when arriving on site including washing hands and using hand sanitiser. Hand sanitisers will also be available for both staff and participants to use at the beginning and completion of each exercise session, or during exercise sessions if required. The equipment (handles) will be regularly cleaned using detergent solution/disinfectant spray or wipes.

### Statistical methods

#### Sample size estimation and justification

This is a feasibility study with the aim of designing, delivering and evaluating a sustainable physical activity program for people living with dementia in residential aged-care. Leith Park residential aged-care facility has approximately 80 residents, with 37 residents living with dementia (diagnosed as mild to severe dementia by a geriatrician). For the pilot study, we aim to recruit 12 participants for each group. We anticipate 3–4 exercise groups, with a total of 24 participants overall (20 participants completing the study allowing for ~ 15% drop out rate). Our previous trial had 11% drop out from the exercise intervention group [17]. The targeted sample is feasible to be recruited and then followed up for 6 months to allow completion of the trial. The targeted number is also sufficient to provide preliminary results about the feasibility and safety of the exercise program to then optimise it for people living with dementia.

It should be noted that the study is not powered for significant changes in the secondary measures, but that the data from this study will inform sample size calculation for a future large multi-site cluster randomised trial.

### Statistical analysis

Data for the feasibility and safety components of the study will be analysed as follows (mean, standard deviation and proportion): proportion of participants approached to participate who did commence the program, percentage of participants who complete the intervention, overall percentage of sessions attended, number of participants who dropout, any falls that occur during the exercise sessions, any muscle/joint pain during or after the exercise sessions, and serious adverse events requiring medical attention. Modifications of the exercise program will be reported and a recommended refined structure will be presented at the end of the program.

An acceptable level for feasibility of the program will be based on the following: ≥ 70% adherence of the prescribed number of exercise sessions [24] at the 12-week structured exercise program completion, and a ≥ 60% adherence for the overall 6-month exercise program, with retention of 85% of the sample (estimate 15% drop out).

To determine statistical trends of effectiveness, analyses of the selected outcomes such as cognitive, physical function, quality of life and social measures will be performed to assess the changes within and between groups over time (pre/post). Repeated measures ANOVA with factors of intervention (Seniors Exercise Park program, control) and time (pre-post intervention and follow-up) will be used. A post hoc analysis will be undertaken using the group differences and variability within groups on the secondary measures to determine the required sample size for a future adequately powered study using these outcomes.

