#### Secondary outcomes

A comprehensive suite of physical function (strength, balance, functional mobility), psychosocial (quality of life, depression, loneliness), cognitive, and falls risk and falls history will be assessed. Physical activity participation, engagement, social interaction, mood and enjoyment data will also be collected.

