#### Physical function measures

Physiological measures of strength, balance and functional mobility will be assessed using the following validated tests:(i)Functional lower limb muscle strength using the five times sit to stand test [25]. Participants will be asked to sit on a chair (43 cm high) and stand up (with arms crossed over their chest) five times. The time taken to complete the sit to stand will be measured (seconds).(ii)Exercise tolerance and functional mobility using the two-minute walk test [26]. Participants will walk in a marked area for 2 min at their comfortable pace. The distance covered during the 2 min will be recorded. The length of walkway will be around 10–15 m, based on available length of the facility corridor.(iii)Dynamic balance using the step test [27]. Participants will be asked to place one foot onto a 7.5cm-high step and then back down to the floor repeatedly as fast as possible for 15 s. The number of steps completed in the 15s period for each leg will be recorded. The step test is a test of dynamic standing balance, only takes approximately 1 min to administer, has been shown to have good retest reliability (ICC = .868) in people living with dementia [28], and demonstrated significant improvement in another Seniors Exercise park study (ENJOY translation study) in older people without cognitive impairment [19].(iv)Walking speed using the 4 meters walk test [29]. Participants will be asked to walk 4 m at their usual walking pace. Gait speed will be defined by distance (in meters) divided by time (in seconds). Participants will start walking 2 m before the 4m walkway, and finish walking 2 m after the 4m walkway.

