#### Psychosocial, cognitive and quality of life health outcomes

A set of valid, reliable and widely used instruments (specifically for older people and those living with dementia) for cognitive screening, quality of life, socialisation, daily activity engagement and depression will be used.(i)*The Montreal Cognitive Assessment (MoCA)* is a brief 30-question cognitive screening test. It assesses several cognitive domains: attention and concentration, executive function, memory, language, visuoconstructional skills, conceptual thinking, calculations and orientation [30].(ii)*Health-related quality of life* will be assessed using two instruments: the Quality of Life in Alzheimer's disease scale (QoL-AD) and the EQ-5D-5L. The QoL-AD will be administered via interview with the person and is comprised of 13 items (physical health, energy, mood, living situation, memory, family, marriage, friends, self as a whole, ability to do chores, ability to do things for fun, money and life as a whole) [31]. The EQ-5D-5L is a generic instrument to assess health related quality of life that comprises five dimensions (mobility, self-care, usual activities, pain/discomfort and anxiety/depression) as well as overall utility score. The EQ-5D-5L allows comparison across multiple populations [32], and is the most widely published and used health utility scale for which there are multiple utility conversions available for populations internationally.(iii)*Fear of falls* will be assessed using the Iconographical Falls Efficacy Scale [33]. The IFES is a valid and reliable 10 items scale that assesses fear of falling in older people with cognitive decline.(iv)*Loneliness* will be assessed using the UCLA 3-Item Loneliness Scale. The UCLA Loneliness Scale includes three dimensions of loneliness: relational connectedness, social connectedness and self-perceived isolation [34, 35].(v)*Depression* will be assessed using the short version Geriatric Depression Scale (GDS-15) [36]. The GDS-15 is a 15-item instrument where a score of 0 to 5 is considered normal and a score greater than 5 suggests depressive symptoms.(vi)*Social isolation and social support* will be assessed using the short version 6 items Lubben Social Network Scale (LSNS-6) [37]. The score ranges between 0 and 30 where higher scores indicate more social engagement(vii)*Engagement with daily activity* will be assessed by aged-care staff using the Pool Activity Level (PAL). The PAL is a widely used, validated, measure of engagement with activity for older people living with dementia [38]. The researchers/aged-care staff will rate residents’ ability to plan and perform during nine common daily activities—bathing/washing, dressing, eating, contact with others, group work skills, communication skills, practical activities, use of objects, reading/looking at a newspaper/magazine. Each activity is scored on a 4-point scale: 1 = ‘planned—needing little or no help with everyday activities’; 2 = ‘exploratory—able to carry out familiar activities in familiar surroundings’; 3 = ‘sensory—limited ability to perform an activity’; 4 = ‘reflex’—unable to perform basic everyday tasks without assistance’. The caregiver ticks the one that most accurately describes the individual’s performance of that activity over the preceding two weeks.

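### The plan looks for trends of effectiveness by testing an open set of secondary measures (13 instruments, no lead measure) in about 20 completers; it should estimate differences instead

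*Protocol article*

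**What the plan says.** The Statistical analysis section gives the purpose and scope of the secondary analysis as "To determine statistical trends of effectiveness, analyses of the selected outcomes such as cognitive, physical function, quality of life and social measures". These analyses "will be performed to assess the changes within and between groups over time (pre/post"). The method is fixed: "Repeated measures ANOVA with factors of intervention (Seniors Exercise Park program, control) and time (pre-post intervention and follow-up) will be used". The same section then uses the observed group differences and variability on the secondary measures to size a later study.

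The measures come from three lists:
- **Physical function measures:** four tests (five times sit to stand, two-minute walk, step test, 4 m walking speed).
- **Psychosocial, cognitive and quality of life health outcomes:** eight instruments (MoCA, QoL-AD, EQ-5D-5L, IFES, UCLA 3-item, GDS-15, LSNS-6, PAL).
- **Falls risk assessment:** one instrument (FRAT).

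None is named as the lead.

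Two caveats are given. Sample size estimation and justification says that "the study is not powered for significant changes in the secondary measures". The Discussion calls the secondary results preliminary and intends them to inform a fully powered study. Primary outcome and Statistical analysis make feasibility, safety and supervision primary, with separate acceptance levels for adherence (70% and 60%) and retention (85%).

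**The concern.** The stated purpose is to find signals of effectiveness by testing, and the wording leaves open which measures enter. With many measures and no lead, some nominally positive results are expected by chance even if the programme does nothing.

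The caveat about power warns the reader about effects that may be missed. It does not address results that are positive by chance.

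Within-group change adds to the problem. A pre-post change in the exercise arm makes no use of the control arm, so it cannot show that the programme caused it.

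Two things are at stake: what the pilot report may say about preliminary benefit, and which measure attracts attention when the larger trial is designed.

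**Working it through.** **Inputs from the protocol.** 12 per group, 24 in total, 20 completing at about 15% dropout (Sample size estimation and justification). Check: 20 / 0.85 = 23.5, rounded up to 24; and 24 × 0.85 = 20.4. The plan's figure reproduces. I use 10 completers per group.

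**Number of measures.** 4 + 8 + 1 = 13. This leaves out falls history and the per-session scales, and counts the step test once although it is recorded for each leg.

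**Inputs the protocol does not give (assumed).** Significance level 0.05, with 0.10 as a looser reading of a trend; equal correlation between measures of 0, 0.3, 0.5 or 0.7; within-person correlation 0.7 across the three visits; no effect and no drift over time.

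**Independent measures, one test each.** Chance of at least one positive = 1 − (1 − α)^k.
- α = 0.05, k = 13: 1 − 0.95^13 = 48.7%.
- α = 0.10, k = 13: 1 − 0.90^13 = 74.6%.
- One lead measure, k = 1: 5% or 10%.

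**Correlated measures.** Null trials were simulated with 10 per group, three visits, 13 measures and 4,000 runs per setting. Chance of at least one positive result:

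| What counts as positive | corr. 0 | 0.3 | 0.5 | 0.7 |
|---|---|---|---|---|
| Group × time test, 0.05 | 49% | 43% | 33% | 26% |
| Between-group pre-post difference, 0.05 | 49% | 42% | 34% | 25% |
| The same difference, only if it favours the programme | 28% | 22% | 17% | 12% |
| Group × time test, 0.10 | 75% | 68% | 55% | 41% |
| Group × time, or within-exercise-group pre-post, 0.05 | 72% | 64% | 53% | 41% |

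The rate per single group × time test at 0.05 was 4.8% to 5.0%, so the simulation is calibrated. Combining the 0.10 level with within-group tests gives 92%, 86%, 77% and 62%, but that stacks two assumptions and I do not use it as the headline.

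**Why a chance positive could mislead the next design.** With 10 per group, a two-sample t test (18 degrees of freedom, critical value 2.10) reaches p<0.05 only if the observed standardised difference is at least 2.10 × √(2/10) = 0.94. Any measure picked because it was significant will therefore show a large observed difference, whatever the truth.

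**The case against.** The strongest case on the other side has five parts.

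1. **Nothing is decided by these tests.** Acceptance rests on adherence and retention. This stands. A reader might infer a rule under which any positive secondary test means success, but the protocol contains none.
2. **Chance positives are not shown to be the majority outcome.** A reader might infer that a useless programme would show a trend more often than not. With one between-group test per measure at 0.05, the figure never passes 48.7% analytically and falls with correlation. It exceeds half only if p<0.10 is taken as a trend or within-group tests are counted, and in either case only up to a correlation of about 0.5. The protocol sets no level for a trend. Two-sided positives also include results favouring control, which nobody would call effectiveness. This stands.
3. **Thirteen may be too many.** The four domains named in the analysis text could be read as nine measures: one cognitive, four physical, two quality of life, two social. Then 1 − 0.95^9 = 37% if independent. That is a fair reading, but the list is given by example, so the other instruments are not excluded. Nor does the text say that selection would follow the data; it only leaves that possible.
4. **Missing detail may sit in an analysis plan.** The significance level, a closed list and multiplicity handling are commonly left to one, and only the article is at hand. Their absence alone would be no finding. What remains is stated text: testing for trends of effectiveness is the purpose given.
5. **The caveats limit the claim.** The statement on power and the word preliminary do soften it. Neither deals with chance positives. Nothing says the future endpoint will be whichever measure shows a trend, so that harm is a risk and not a plan.

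**Conclusion.** The point holds in a limited form. Testing an open set of secondary measures for trends of effectiveness, with no lead measure and about 20 completers, gives a chance of at least one false nominal positive well above 5%:
- about 25% to 49% for one between-group test per measure at 0.05;
- about 12% to 28% if only results favouring the programme count;
- about 40% to 75% if a trend means p<0.10 or if tests within the exercise group also count.

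All three ranges rest on 13 measures, 10 completers per group, and assumed values for the significance level and the correlation (0.7 down to 0). The pilot's feasibility conclusion is unaffected. What is affected is any statement of preliminary benefit, and possibly the choice of endpoint for the later trial. This is worth changing, but it does not threaten the trial's primary purpose.

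**What to change.** In Statistical analysis, replace the aim of determining trends of effectiveness with estimation:
- For every listed secondary measure, report the between-group difference at 3 and at 6 months with a 95% confidence interval, all in one table.
- Make no trend claim based on a p-value, and no claim of effectiveness from within-group change.
- Do not select measures after the data are seen.
- State in advance that a future endpoint will not be chosen because it showed a trend. Completion rate, floor and ceiling effects, and standard deviation are suitable grounds instead.

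The cost is a change of wording and one full table. No further participants, visits or data are needed. The downside is that the pilot can no longer headline a significant or trend result.
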